### Eligibility Criteria

All participants will be required to sign an informed consent form before the final determination of their eligibility to enroll in the study. Participants will be eligible for inclusion if they:

Are adults with a major depressive episode with a score greater than 34 (signifying severe depression) on the Montgomery-Åsberg Depression Rating Scale (MADRS)Have ultratreatment-resistant MDD (defined as failure to remit despite adequate trials with 5 antidepressants at clinically effective doses, failure to remit with ECT, or failure to remit with ketamine).

Participants will not be eligible for inclusion if they:

Are currently diagnosed with psychosis, an addiction disorder (other than nicotine), borderline personality disorder, or antisocial personality disorder, as these conditions could interfere with adherence to the study protocolAre currently using a herbal compound or an agent known to modulate NMDA (N-methyl-D-aspartate) receptors, as these substances could interfere with the induction of LTP and thereby limit the effectiveness of tDCSAre pregnant, as tDCS has not been adequately studied in this populationHave an electronic implant, cardiac dysrhythmia, seizure disorder, neurological disorder, or neurosurgical history, as the safety of electrical stimulation with tDCS cannot be assured given these comorbidities.

### Participant Recruitment and Randomization

Participants will be recruited from the inpatient population at the Grey Nuns and University of Alberta Hospitals in Edmonton, Alberta. In addition, outpatients in the city and surrounding areas will also be eligible for inclusion. Edmonton is a large and diverse Canadian city, with a metropolitan population of more than 1.3 million people. Participants may contact the study personnel directly or may be referred by their treating clinician; in the latter case, they must first give consent to disclose contact information to the study coordinators, who will then contact the participant and discuss the trial further. In cases where the treating clinician is also a study coordinator, the informed consent process will occur with a separate coordinator. Participants will be informed that they may withdraw their consent, without penalty, at any time and that this will not affect the care they receive from their treating clinician. Consent cannot be withdrawn after the conclusion of the protocol due to the blinding of participant-identifiable data.

Before randomization, participants will undergo a routine history and physical examination and complete the Edinburgh Handedness Inventory [26]. They will also be interviewed by a member of the research team using the Mini International Neuropsychiatric Interview [27]. This validated, structured tool facilitates the diagnosis of the 17 most common psychiatric pathologies and will provide confirmation that participant diagnoses fall within the acceptable purview of the inclusion and exclusion criteria. Participants will also complete a version of the Massachusetts General Hospital Antidepressant Treatment History Questionnaire, modified with the trade names of Canadian drugs [28]. To ensure that the information obtained is as accurate as possible, research personnel may also augment answers on this scale using historical medication information from a participant’s electronic health record. Finally, participants will have their baseline MADRS score recorded to ensure that it is higher than the threshold required for trial participation.

Once the study personnel confirm that participants satisfy the inclusion and exclusion criteria, they will be automatically assigned to a treatment arm using the Research Electronic Data Capture (REDCap) software, hosted at the University of Alberta [29,30]. Randomization will be performed in a permuted block fashion based on a sequence generated by the Robust Randomization App (RRApp) [31]. This sequence will not be known to the study team so as to preserve allocation concealment.

### Intervention and Control

In addition to continuing their usual pharmacological and psychological treatments, participants in both arms will receive 30 sessions of either sham or active tDCS, 5 days per week, for a total of 6 weeks, using a Sooma stimulator (Sooma Oy). This constitutes twice the number of treatment sessions as that used in the longest previously conducted study of tDCS in treatment-resistant depression [20]. For both groups, the anode will be positioned over the left DLPFC (position F3 on the 10-20 EEG system), and the cathode will be positioned over the right DLPFC (position F4). Electrodes will be positioned using the caps supplied by Sooma, with participant head circumference measured first to ensure that the proper-sized cap is applied. Each electrode pad will be saturated with 15 mL of normal saline before application.

Participants will be blinded to the group to which they have been assigned. Two stimulators labeled only as *A* and *B* will be set to provide either sham or active stimulation by an investigator not involved in participant interaction or data collection. In the sham group, the applied current will ramp up from 0.3 mA to 2 mA over 17 seconds and then ramp down to 0.3 mA over 17 seconds, where it will be maintained for the duration of the 30-minute session. Previous trials have demonstrated that this short period of active stimulation is an effective way of triggering scalp tingling at a total dose of tDCS believed to be below the threshold for inducing neuroplasticity changes [32,33]. Current must be maintained at 0.3 mA to allow for operation of the electrode-contact sensors; if these were deactivated entirely, blinding would be broken. In the active intervention group, the applied current will ramp up to 2 mA over 17 seconds and be maintained at that level for 30 minutes, before gradually ramping down.

Participants will be withdrawn from the study if they miss two consecutive treatments or more than five treatments in total, if they undergo a serious adverse event or clinical deterioration (which may include new-onset psychosis, severe suicidal ideation, or a manic or hypomanic switch), or if they or their treating psychiatrist wish them to be withdrawn.

In the unlikely event that a participant undergoes clinical deterioration or that their treating clinician requests their blind be broken, the sole unblinded investigator can be contacted to reveal the treatment code. If the treating clinician is also a study investigator and becomes unblinded as a result of this process, they will be required to recuse themselves from further data collection.

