### Outcomes

The primary outcome will be the change on the MADRS, a 10-item, validated, observer-administered scale of depression severity, which has been extensively used in trials of depression treatment [34]. Investigators will use a structured interview guide when administering the MADRS to improve inter-rater reliability [35].

Secondary outcomes will include the change on the Quick Inventory of Depressive Symptomatology (QIDS-SR-16), a 16-item, participant-administered scale of depression severity, and the World Health Organization Disability Assessment Schedule (WHODAS 2.0), a 12-item measure of functional impairment [36,37]. Cognitive impacts of treatment will be assessed using the Screen for Cognitive Impairment in Psychiatry (SCIP) [38]. The SCIP has been well validated as a tool for measuring cognitive change in patients with depression and other psychiatric illnesses; is brief and relatively simple to perform; and includes a verbal list learning task, working memory test, verbal fluency test, delayed learning task, and visuomotor tracking test. Exploratory analyses will investigate the effect of treatment on language abilities by change in performance on an auditory lexical decision task, in which participants must differentiate real from fictitious words [39,40]. An exploratory acoustic and semantic corpus analysis will also be conducted on the recorded entrance and exit interviews.

Treatment-related manic or hypomanic switches will be captured using the Young Mania Rating Scale, an 11-item observer-administered scale of mania intensity [41]. Other treatment-related side effects will be measured using a scale derived from a systematic review of tDCS-related adverse events [42]. This scale has the benefit of asking participants to comment on the relatedness of their symptoms to their treatment and may help to distinguish between the likely side effects of tDCS and symptoms participants had before the intervention. It has also been used in other randomized control trials evaluating tDCS [43]. In addition, side effects that may be secondary to concurrent medication use will be captured using the Frequency, Intensity, and Burden of Side Effects Rating Scale and the Patient-Rated Inventory of Side Effects Scale [44,45]. Side effects captured through the use of the aforementioned scales will be summarized in an adverse events form, with additional documentation completed on any adverse events deemed to be serious in nature.

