### Data Collection

Measurements for most scales will be conducted at the beginning of the trial (T0), after every 10 sessions (T10, T20, and T30), and 1 month after trial completion (T60; Table 1). Trained psychiatrists, psychiatric residents, and/or medical students will complete all assessments. Data will be collected directly using the REDCap electronic data capture tools.

Recorded entrance and exit interviews will be stored in an encrypted database and have identifying information stripped from them on a rolling basis. This database may then be analyzed in future studies.

Participants will perform the auditory lexical decision task on tablet devices using a previously developed app. They will first answer questions on their age, handedness, native languages, other spoken languages, age at which they began to learn English, English-speaking countries they have visited, and whether or not they grew up in western Canada. They will then hear a series of 200 stimuli and must mark whether they think each stimulus is a real or fictious word. There are a total of 2000 words split into 32 different lists. Participants will perform this task before commencing treatment (T0), after each stimulation session (T1-30), and 1 month after trial completion (T60).

There are 3 validated versions of the SCIP. To prevent participants from improving their scores by way of repeated exposure, version 1 will be administered at baseline, version 2 after the 30 treatments are delivered, and version 3 at the 1-month postcompletion assessment.

**Table 1 table1:** Schedule of assessments.

Assessment			Timepoint								
			Enrollment and baseline^a^		Treatment period^b^						Follow-up^c^
			T0		T1-9; T11-19; T21-29		T10; T20		T30		T60

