### Data Analysis and Sample Size Calculations

The primary and secondary efficacy outcomes will be analyzed using a mixed effects repeated measures ANOVA (analysis of variance), with the study group and time as fixed factors and participants as random factors, based on the intention to treat principle. Due to the wide variety of potential adverse events that can be captured, we will present this information as frequency data.

To detect a moderate effect size for the primary outcome, represented by a Cohen *f* of 0.25, with a power of 80% and significance ⍺=.05, we estimate that 60 participants will need to complete the protocol. This assumes a moderate correlation (*r*=0.3) between time points, using the power curves described in the textbook by Kirk [46]. As a study of this scope, in the ultraresistant MDD population, has not been performed before, we are unable to estimate the dropout rate. We plan to conduct an interim analysis after 30 participants complete the protocol. We will analyze the main effects of the treatment by presenting the significance of the time, treatment group, and interaction terms in the ANOVA. If there is a significant interaction, we will conduct posthoc comparisons between mean treatment and placebo outcome scores, at each time point, to characterize this effect further and will use the Tukey method to control the familywise error rate.

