### Limitations

This study also has several practical limitations that may affect the results. With regard to treatment modality, delivering tDCS in a hospital setting will impose a minimal burden on inpatients, but outpatients will have to be functional enough to arrange for transport to the hospital on a daily basis. As such, there is a risk that the study population may miss outpatients with severe depression. The need for daily travel to the hospital can also pose problems with participant compliance. We may use home-based tDCS in future studies to mitigate this, although funding limitations prevented us from employing this approach in the NESBID trial. Second, our blinding procedure follows that used in most other studies of tDCS, but recent evidence suggests that this may not sufficiently mitigate the placebo effect. Turi et al [51] showed that healthy volunteers were able to distinguish the *fade-in, short stimulation, fade-out* method of sham stimulation, described above, from true active stimulation at a level significantly greater than chance. It is not yet known how generalizable these findings are to a population with depression, but there is a need for more research into alternative methods of blinding in tDCS studies.

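### Withdrawal from the study, rather than from stimulation only, for missed sessions or deterioration undermines the declared intention-to-treat analysis

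*Protocol article*

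**What the plan says.** Under Intervention and Control: "Participants will be withdrawn from the study if they miss two consecutive treatments or more than five treatments in total". The same sentence adds withdrawal "if they undergo a serious adverse event or clinical deterioration", giving new psychosis, severe suicidal ideation and a manic or hypomanic switch as examples. It also allows withdrawal at the wish of the participant or the treating psychiatrist. What the participant leaves is the study; stopping stimulation is not treated as a separate step.

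Under Outcomes: "The primary outcome will be the change on the MADRS". Under Data Collection, most scales are rated at baseline, "after every 10 sessions (T10, T20, and T30), and 1 month after trial completion". At five sessions a week, ratings during treatment are two weeks apart.

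Under Data Analysis and Sample Size Calculations, efficacy outcomes go into a mixed effects repeated measures ANOVA "with the study group and time as fixed factors and participants as random factors", "based on the intention to treat principle".

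Under Limitations: "The need for daily travel to the hospital can also pose problems with participant compliance".

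**The concern.** Intention to treat needs two things: that participants are analysed in the arm to which they were randomised, and that their outcomes are sought whatever treatment they received. The withdrawal rule puts the second in doubt. Some of its triggers, namely deterioration and serious adverse events, are themselves bad outcomes or close to them, and their frequency may differ between active and sham. A participant who deteriorates at session 12 would leave after the T10 rating and before T20, so the worsening would never be scored.

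At stake is the primary comparison at the later time points, where observed MADRS scores would come only from participants who had not been withdrawn. This is not a detail that can wait for an analysis plan. An analysis plan decides how collected data are used; it cannot restore ratings that were not taken.

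**Working it through.** **1. The plan's own figure.** The article asks for 60 completers, with Cohen f = 0.25, 80% power, alpha 0.05 and r = 0.3. For the between-group effect with N participants and m time points, the noncentrality is λ = f²·N·m / (1 + (m − 1)·r), on 1 and N − 2 degrees of freedom. With N = 60 and m = 5, λ = 0.0625 × 60 × 5 / 2.2 = 8.52 and power is 81.9%; the smallest even N reaching 80% is 58. With m = 4, power at 60 is 78.9% and the N needed is 62. The stated 60 is therefore reproduced. It counts completers, the Abstract gives the same 60 as the target, and no dropout rate is assumed.

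**2. How far the missed-session rule could reach.** The article gives no miss rate, so p, the chance of missing any one session, is an assumption, as is independence between sessions. For the two-in-a-row trigger alone, the chance of remaining after n sessions is q(n) = (1 − p)·q(n − 1) + p(1 − p)·q(n − 2), with q(0) = q(1) = 1. The full rule is a chain over 30 sessions that tracks whether the last session was missed and how many have been missed so far. A participant leaves at a second consecutive miss or at the sixth miss.

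| p (assumed) | two in a row only | full rule |
|---|---|---|
| 5% | 6.7% | 6.8% |
| 7.5% | 14.2% | 14.8% |
| 10% | 23.5% | 25.3% |
| 15% | 44.3% | 50.2% |

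Most of the reach comes from the two-in-a-row trigger. Stopping the same chain earlier at p = 10% gives 8.0% withdrawn by session 10 and 16.2% by session 20, so the loss builds up towards T20, T30 and T60.

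**3. What the mixed model can and cannot recover.** This is a large-sample illustration in which every input is assumed: five visits, SD 10, r = 0.3, no treatment effect apart from withdrawal, withdrawn participants 8 points worse from that time on, and withdrawal spread evenly over T10, T20 and T30. The target is the active-minus-sham MADRS difference at T30 in everyone randomised.

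With 25% withdrawn on active and 15% on sham, the target is (0.25 − 0.15) × 8 = 0.8 points, active worse.

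| Situation | full follow-up | likelihood-based, scores up to withdrawal | non-withdrawn only |
|---|---|---|---|
| worsening never rated | 0.79 | 0.01 | 0.01 |
| worsening rated at one visit before leaving | 0.82 | 0.50 | 0.01 |

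In the first row the model misses the whole difference, to the advantage of active. In the second it recovers more than half. Swapping the two withdrawal rates reverses the sign. With 20% withdrawn in each arm, full follow-up and likelihood-based estimates are both within 0.03 of zero, so no bias appears.

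**4. The texts side by side.** The withdrawal rule ends participation; the analysis section promises intention to treat; the assessment schedule has no visit for a participant who has left. No sentence links the three.

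**The case against.** The strongest reply is that the article does not say ratings stop. A reader might infer that later MADRS scores are never collected. That is the plain meaning of leaving the study, but it is not stated, and a fuller protocol could provide otherwise. This stands as a limit on wording. It does not remove the point, because the article states a positive rule and nothing in it softens that rule.

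A reader might also infer that the trial becomes an analysis of adherers, or that the damage is beyond repair in analysis. The documents support neither. The specified model can keep every randomised participant's scores up to withdrawal, in the assigned arm, and nothing says those scores are dropped. It is valid if missingness depends only on scores already observed. Step 3 shows partial recovery when worsening is rated once, and no bias when withdrawal is equal between arms.

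A simple bias formula for a completers' mean (difference in withdrawal rates times how much worse the withdrawn are) would not describe this trial, because no such mean is planned.

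Three further objections stand in part. Missed sessions caused by transport are not shown to be related to outcome, so the bias argument fits the deterioration trigger best. The Limitations section expects little burden for inpatients, so one miss rate for all participants is crude. And the treatment code may be revealed after deterioration, so later observer ratings could be unblinded unless this is planned for.

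**Conclusion.** The point holds in this form. Read plainly, the withdrawal rule loses MADRS scores after withdrawal, mainly at T20, T30 and T60, for reasons that include poor outcome, and this undermines the declared intention-to-treat analysis. The mixed model protects against it only in part: it can be biased when deterioration triggers removal between ratings and withdrawal differs by arm.

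The size and direction of any bias cannot be derived from the article; the 0.8 points above is an illustration on assumed inputs. The reach of 7% to 50% rests on assumed, independent miss rates of 5% to 15%. It describes how many participants the missed-session rule could remove, not bias in the result. The change should be made before enrolment, because ratings not taken cannot be recovered later.

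**What to change.** Reconcile Intervention and Control with Data Analysis and Sample Size Calculations by separating discontinuation of stimulation from withdrawal from the study.

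- Unless consent is withdrawn, keep collecting MADRS, QIDS-SR-16 and WHODAS 2.0 at the times when T10, T20, T30 and T60 would have fallen: weeks 2, 4 and 6, and one month later.
- Where the code has been broken, use raters who remain blinded.
- State that these data enter the primary intention-to-treat analysis.

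The criteria for stopping stimulation remain a clinical matter and need no change for this purpose.

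The cost is a short amendment, revised consent wording and a few extra ratings by existing staff. Some ratings may be hard to obtain from participants who have deteriorated, so some missing data will remain.

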### Outcomes

The primary outcome will be the change on the MADRS, a 10-item, validated, observer-administered scale of depression severity, which has been extensively used in trials of depression treatment [34]. Investigators will use a structured interview guide when administering the MADRS to improve inter-rater reliability [35].

Secondary outcomes will include the change on the Quick Inventory of Depressive Symptomatology (QIDS-SR-16), a 16-item, participant-administered scale of depression severity, and the World Health Organization Disability Assessment Schedule (WHODAS 2.0), a 12-item measure of functional impairment [36,37]. Cognitive impacts of treatment will be assessed using the Screen for Cognitive Impairment in Psychiatry (SCIP) [38]. The SCIP has been well validated as a tool for measuring cognitive change in patients with depression and other psychiatric illnesses; is brief and relatively simple to perform; and includes a verbal list learning task, working memory test, verbal fluency test, delayed learning task, and visuomotor tracking test. Exploratory analyses will investigate the effect of treatment on language abilities by change in performance on an auditory lexical decision task, in which participants must differentiate real from fictitious words [39,40]. An exploratory acoustic and semantic corpus analysis will also be conducted on the recorded entrance and exit interviews.

Treatment-related manic or hypomanic switches will be captured using the Young Mania Rating Scale, an 11-item observer-administered scale of mania intensity [41]. Other treatment-related side effects will be measured using a scale derived from a systematic review of tDCS-related adverse events [42]. This scale has the benefit of asking participants to comment on the relatedness of their symptoms to their treatment and may help to distinguish between the likely side effects of tDCS and symptoms participants had before the intervention. It has also been used in other randomized control trials evaluating tDCS [43]. In addition, side effects that may be secondary to concurrent medication use will be captured using the Frequency, Intensity, and Burden of Side Effects Rating Scale and the Patient-Rated Inventory of Side Effects Scale [44,45]. Side effects captured through the use of the aforementioned scales will be summarized in an adverse events form, with additional documentation completed on any adverse events deemed to be serious in nature.

